### Masking

Interviewers, statisticians, economists, PSC and DMEC will be masked to participants’ allocations between the two groups. However, masking participants and DSPs is not possible. To minimise the risk of bias [36], several precautions are taken:The fieldwork manual for interviewers and support staff at each site explains the case for masking and its importance.Site coordinators are asked to deny interviewers access to allocations, for example in the recruitment log.All staff are asked to minimise participant-specific discussion.Deliberate disclosure of participants’ allocations is limited to serious adverse events or safeguarding issues.All cases of unmasking - by participants, interviewers, clinical or support staff or researchers - are recorded, including the reason for unmasking.Masked interviewers record after each interview to which group they judge the pair belong and with how much confidence.Statistical tests will be undertaken to determine whether, and if so how, unmasking implicitly or explicitly affects estimated parameters.

### Data management

Personal information will be held securely in accordance with data protection legislation. Screening forms completed by clinic staff and questionnaires completed by interviewers will be transferred to the TM by encrypted NHSmail. Unmasked researchers supervised by the TDM based at STU enter data into MACRO4 electronic data collection system provided by Elsevier (2017) [37] in accordance with the study-specific handbook [38]. Participants’ trial numbers will be used to link their data and ensure they remain anonymous. A full audit trial will be maintained by recording all amendments to data with the reason and the time of amendment. Thus, the Sponsor may also inspect or audit the study at any time. The STU will compile the final trial dataset in MACRO4 and transfer it to the PSSRU only when it is complete.

### Sample size

An analysable sample of 360 (180 in each group) across participating Trusts would yield 80% power to detect an effect size (standardised mean difference) of 0.30 on BADLS when using a two-sided significance level of 5%. To allow for 25% attrition (estimated from previous similar studies) between baseline and final interviews the aim is to recruit 480 randomised pairs of people with mild to moderate dementia and an identified carer.

### Process evaluation

The Medical Research Council advocates process evaluations within trials of complex interventions to assess implementation and identify contextual factors associated with variation in outcomes [39]. To replicate the DESCANT intervention will need understanding of how it works in the intervention group. Figure 4 shows the process evaluation framework comprising a mix of standardised [40–42] and study-specific measures. Data are also collected from participants about appropriateness and timeliness and from DSPs about barriers and facilitators to implementation and future roll-out.

**Fig. 4 Fig4:**
[figure not shown]
Process evaluation framework for intervention group

### Qualitative data collection

To enhance evaluation of its intervention, DESCANT includes a qualitative component. Audio-recorded structured interviews of a sub-sample of participating pairs will provide richer contextual and conversational data about participants’ experiences and assessments of the role of aids in combating memory loss. These data will be collected unobtrusively at baseline interview [43].

Participants will be included from the intervention and comparator groups to avoid unmasking of interviewers by the research team and ensure potential bias from audio-recording affects each group equally. The sample size will be set according to practical criteria like available resources and time and when data saturation is achieved [44]. It is predicted that this will need a judgement sample of at least 15 participants identified sequentially from the baseline sample.

### Statistical analysis

Analysis will follow a defined statistical analysis plan approved by the DMEC before data are accessed. Baseline characteristics of participants will be presented. Continuous variables will be reported by means and standard deviations and categorical variables by counts and percentages. Analyses by treatment allocated will estimate the effect of the intervention on participants, using analysis of covariance to adjust for baseline differences in demographic characteristics, comorbidities, time since first attendance at memory clinic or equivalent and for the interval until follow up. Primary analysis will focus on BADLS scores at 26 weeks. Secondary analysis will take account of the content of, and adherence to, the intervention to explore the effect of compliance on BADLS scores.

To explore whether people with dementia who have particular characteristics are more likely to use specific aids, logistic regression will be used. To identify which participants are more likely to benefit from this intervention, linear regression will be used to relate change in BADLS scores at 26 weeks to similar covariates.

Whether the inevitable missing data cause bias will be investigated. If predictors of missing data are identified that are related to outcomes, multiple imputation to adjust for these biases will be used.

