**Methods/design:**

This is a multi-site, pragmatic randomised trial preceded by a feasibility study and internal pilot. We aim to allocate at random 360 pairs comprising a person with mild to moderate dementia and an identified carer between the DESCANT intervention and treatment as usual. We assess participants at baseline, 13 and 26 weeks. The primary outcome measure is the Bristol Activities of Daily Living Scale; other participant outcomes include cognition, quality of life, activities of daily living and social networking; carer outcomes include quality of life, sense of competence and mental health. To enhance this quantitative evaluation we are conducting a qualitative component and a process evaluation to assess the implementation process and identify contextual factors associated with variation.

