#### Random allocation

The Trial Manager (TM) coordinates recruitment from all sites and forwards details to STU through their email-based randomisation service. After baseline interviews, the unmasked Trial Data Manager (TDM) at STU oversees stratification of people with dementia by Trust, age, gender, whether living with a carer and time since first attendance at memory clinic or equivalent. Allocation between intervention and comparator groups using dynamic software randomises participants in real time, thus preventing subversion while ensuring (stochastic) balance between the two groups [35].

The person with dementia receives a letter specifying their allocated group and reminding them what this entails. Those in the comparator group receive a general guide to dementia [13]. The intervention group receive confirmation of arrangements for an initial visit by the DSP after about 2 weeks.

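### The listed ANCOVA covariates omit baseline BADLS, so the 26-week BADLS comparison as written gives up precision that the trial could have at no cost

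*Protocol article*

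**What the plan says.** The Statistical analysis section of the protocol article describes treatment-effect analyses "using analysis of covariance to adjust for baseline differences in demographic characteristics, comorbidities, time since first attendance at memory clinic or equivalent". Time to follow-up is the last covariate named. Nothing marks these four items as examples. The next sentence sets the outcome: "Primary analysis will focus on BADLS scores at 26 weeks", which is a follow-up score and not a change.

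Baseline BADLS is not named as a covariate anywhere in the article. The Random allocation section describes "stratification of people with dementia by Trust, age, gender, whether living with a carer and time since first attendance at memory clinic or equivalent", so neither BADLS nor dementia severity is a stratification factor.

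The article does indicate that a baseline value exists. The abstract states "We assess participants at baseline, 13 and 26 weeks", the Data collection section describes interviews at the same three times, and the Statistical analysis section plans that "linear regression will be used to relate change in BADLS scores at 26 weeks to similar covariates", which cannot be done without a baseline score. The assessment schedule is in a figure that is not shown, so this is an inference, but a safe one.

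**The concern.** When a scale is measured before randomisation and again at the endpoint, its baseline value is normally the first covariate in an ANCOVA of the endpoint. It usually explains outcome variance that demographics and comorbidities do not. The article names covariates and leaves this one out.

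Two things are at stake, and they are two views of the same loss. The treatment effect has a larger standard error than it needs. And if the groups happen to differ in baseline function, part of that difference is carried into the 26-week comparison. Eligibility spans mild to moderate dementia, so participants can be expected to differ in baseline function. Stratifying by age, living with a carer and time since first attendance may balance it in part, but not directly.

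**Working it through.** **Inputs from the protocol article (Sample size).** The stated target is 360 analysable pairs, 180 per group, and the article says that this number "would yield 80% power to detect an effect size (standardised mean difference) of 0.30 on BADLS". The test is two-sided at the 5% level, with 25% attrition and 480 pairs to be randomised.

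**Assumed, not in the article.** The correlation r between baseline and 26-week BADLS, and that the 0.30 is standardised by the raw 26-week SD (set to 1).

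**Step 1: reproduce the plan's figures.**
- n per group = 2 × (1.960 + 0.842)² / 0.30² = 174.4, so 175 per group or 350 in total. The stated 360 is within 3%.
- Standard error of the difference with 180 per group = √(2/180) = 0.1054. Power = Φ(0.30/0.1054 − 1.96) = Φ(0.886) = 81.2% (81.0% by noncentral t).
- 360 / (1 − 0.25) = 480.

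The sample size stands on its own terms and takes no credit for a baseline correlation.

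**Step 2: add baseline BADLS to a model with no other covariates.** The residual SD is √(1 − r²), so power = Φ(0.30 / [0.1054 × √(1 − r²)] − 1.96).

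| r (assumed) | Variance factor 1 − r² | Power, 180 per group | n per group for 80% power |
|---|---|---|---|
| no adjustment | 1.00 | 81.2% | 175 |
| 0.3 | 0.91 | 84.7% | 159 |
| 0.5 | 0.75 | 90.8% | 131 |
| 0.7 | 0.51 | 97.9% | 89 |
| 0.8 | 0.36 | 99.7% | 63 |

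**Step 3: use the comparator the plan actually has.** The plan already adjusts for four classes of covariate, so only the increment over these counts. Suppose they explain 10% of the variance (assumed). The residual SD is then √0.90, and power is Φ(0.30 / [0.1054 × √0.90] − 1.96) = 85.1%. If adding baseline raises the explained share to R², the residual SD is √(1 − R²):
- R² = 0.30: power 92.5%, variance ratio 0.70/0.90 = 0.78
- R² = 0.50: power 98.1%, variance ratio 0.50/0.90 = 0.56
- R² = 0.60: power 99.4%, variance ratio 0.40/0.90 = 0.44

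**Step 4: chance imbalance.** With 180 per group the difference in baseline means also has standard error √(2/180) = 0.105 SD, so 95% of randomisations fall within ±1.96 × 0.1054 = ±0.207 SD. With no adjustment, a baseline gap g moves the estimate by r × g. At the 95% limit:
- r = 0.3: 0.3 × 0.207 = 0.062 SD, or 21% of the target 0.30
- r = 0.5: 0.103 SD, or 34%
- r = 0.7: 0.145 SD, or 48%
- r = 0.8: 0.165 SD, or 55%

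These shifts average zero over randomisations. The listed covariates would remove part of them to the extent that they predict baseline BADLS.

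**The case against.** The strongest reply is that this is a condensed article. The section opens by deferring to an analysis plan that the monitoring committee approves before data are accessed. The covariate sentence covers every outcome, and a sentence spanning many scales may name only shared covariates, since the baseline score differs for each. The covariates are loose classes, and Trust, a stratification factor, is also absent, so the list may be a summary. Some readers will take the term ANCOVA to imply the baseline outcome.

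Part of this stands. The unseen analysis plan may already include baseline BADLS, and the article does not expressly exclude it. But the article did not leave the covariates open. It named them without open-ended wording, omitted this one, and supplies it nowhere else.

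Four stronger readings are tempting and are not supported:
- A reader might infer that adjusting for baseline differences means choosing covariates after seeing which are imbalanced. The article states no imbalance criterion, and approval of the analysis plan before data access answers the worry.
- A reader might infer that the result would be biased or falsely significant. Under randomisation the omission does neither on average.
- A reader might infer that the trial is underpowered without the baseline score. The stated sample size reproduces at about 81% power with no adjustment.
- A reader might take baseline BADLS to be the strongest predictor, or take the rise from 81% as the gain over the plan. The first is a reasonable expectation that the article does not document; the second compares with a model that has no covariates at all.

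**Conclusion.** The point holds as a matter of efficiency and robustness. Followed as written, the model leaves out a baseline measurement that the trial evidently has and does not stratify on. The cost is a wider confidence interval and an estimate that can carry a chance baseline difference.

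The direction holds for any correlation between baseline and 26-week BADLS beyond what the listed covariates explain. The size rests on assumptions. With the 0.30 in raw 26-week SD units, power at 180 per group goes from 81% with no covariates to 85%, 91% or 98% at r = 0.3, 0.5 or 0.7. Against listed covariates that explain 10% of variance, it goes from 85% to 92.5–99.4% if baseline raises the explained share to 30–60%. If the 0.30 was standardised by a residual or change SD, these gains do not follow as stated. This is worth correcting, but it does not threaten the trial's validity.

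**What to change.** State that the primary model for 26-week BADLS contains treatment group, baseline BADLS as a continuous covariate, and the covariates already listed. State also that each secondary scale is adjusted for its own baseline value. If the analysis plan already says this, one confirming sentence settles the matter.

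The cost is wording in the protocol or analysis plan, settled before data are accessed. It needs no new data, no extra participants and no change to the sample size.

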### Procedure

#### Data collection

Interviewers, who are masked to the allocated group, interview participants face to face at home at baseline and 13 and 26 weeks after first interview. Data quality will be promoted in two ways: interviewers undertake online training (focussing on completing outcome measures) and sites check all documents to minimise missing data.

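### The primary ANCOVA adjusts for the interval until follow-up, which is realised after randomisation; the effect is probably small but easily avoided

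*Protocol article*

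**What the plan says.** All references are to the protocol article.

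- **Statistical analysis**, on the model: "Analyses by treatment allocated will estimate the effect of the intervention on participants, using analysis of covariance to adjust for baseline differences". The listed adjustments are demographic characteristics and comorbidities, then "time since first attendance at memory clinic or equivalent and for the interval until follow up". The next sentence sets the outcome: "Primary analysis will focus on BADLS scores at 26 weeks".
- **Data collection**: masked interviewers "interview participants face to face at home at baseline and 13 and 26 weeks after first interview".
- **Random allocation**: "After baseline interviews, the unmasked Trial Data Manager (TDM) at STU oversees stratification of people with dementia". In the same section: "The intervention group receive confirmation of arrangements for an initial visit by the DSP after about 2 weeks".
- **Masking**: "However, masking participants and DSPs is not possible".
- **Design**: after a 40-participant pilot, follow-up was cut from 12 to 6 months. The pilot data are to be kept and adjusted for that change. Neither this section nor Statistical analysis says whether the interval covariate is the means of doing so.

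**The concern.** An ANCOVA that adjusts only for variables fixed before randomisation keeps the randomised comparison intact. The interval to the 26-week interview is different. It starts at the baseline interview, before allocation, and ends on a date that is settled afterwards. In between, participants know their group and one arm alone receives practitioner visits. Illness or carer strain could delay a home interview, and both are plausibly related to daily functioning.

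There are two routes to a shift. Allocation may change interview timing while timing is also related to deterioration. Or deterioration may cause delay while treatment changes deterioration, so that the interval carries part of the treatment effect and adjusting for it removes that part. In either case the coefficient for treatment no longer estimates the plain effect of being allocated to the intervention, and its confidence interval gives no sign of this.

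This is a covariate that the article names, so it is a stated choice and not a detail left to the statistical analysis plan.

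**Working it through.** **Step 1: timing.** Baseline interview, then randomisation, then (in one arm only) a first practitioner visit after about 2 weeks, then interviews at 13 and 26 weeks from the first interview. The realised interval is therefore a post-randomisation variable.

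**Step 2: the plan's own figure.** Inputs from Sample size: standardised difference 0.30, two-sided 5%, 80% power, 25% attrition.

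- n per arm = 2 × (1.960 + 0.842)² / 0.30² = 174.4, so 175 per arm and 350 in total, against 360 stated.
- With 180 per arm the standard error is √(2/180) = 0.105 SD. Power is Φ(0.30/0.1054 − 1.96) = Φ(0.886) = 81.2%.
- 360 / 0.75 = 480 to be randomised.

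The calculation reproduces, and this point does not affect it.

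**Step 3: size of the shift.** In a linear model with outcome and interval in within-arm SD units,

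adjusted effect = unadjusted effect − r × d_T.

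The protocol gives neither r nor d_T, so all values below are assumptions. The power columns use 180 per arm and residual SD √(1 − r²).

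| r | d_T | shift (SD) | share of 0.30 | power if effect shrinks | power if effect grows | type I error |
|---|---|---|---|---|---|---|
| 0 | any | 0 | 0% | 81.2% | 81.2% | 5.0% |
| 0.1 | 0.1 | 0.01 | 3% | 79.0% | 84.0% | 5.1% |
| 0.1 | 0.3 | 0.03 | 10% | 73.1% | 88.2% | 5.9% |
| 0.2 | 0.1 | 0.02 | 7% | 77.4% | 87.3% | 5.4% |
| 0.2 | 0.3 | 0.06 | 20% | 64.2% | 93.6% | 8.9% |

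The shift is also zero whenever d_T = 0. The largest shift shown, 0.06 SD, is 0.06/0.105 = 0.57 of a standard error.

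**Step 4: simulation by mechanism** (180 per arm, 4,000 replicates; true effect 0.30 except in the null case).

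- *Delay driven only by deterioration, which treatment alters.* With coefficient 0.2, d_T = 0.2 × 0.30 = 0.06, so the expected estimate is 0.30 − 0.2 × 0.06 = 0.288. Simulated: 0.289, power 79%. With coefficient 0.3, expected 0.30 − 0.3 × 0.09 = 0.273. Simulated: 0.271, power 76%.
- *Allocation also moves the interval directly by 0.3 SD, coefficient 0.2.* If this adds to the indirect shift, d_T = 0.36 and the expected estimate is 0.228. Simulated: 0.228, power 58%. If it opposes it, d_T = −0.24 and the expected estimate is 0.348. Simulated: 0.348.
- *No true effect, direct shift 0.3 SD, coefficient 0.2.* Expected −0.06. Simulated: −0.059, type I error 8%.
- *Scheduling only.* Allocation moves the interval by 0.3 SD, deterioration plays no part in delay, and the score drifts 0.05 SD per SD of interval. The unadjusted estimate is expected at 0.30 + 0.3 × 0.05 = 0.315 and the adjusted one at 0.30. Simulated: 0.318 and 0.303. Here the covariate helps.

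So r × d_T is always the gap between the two models. Whether that gap is bias or the removal of a timing artefact depends on why the interval differs, and the data alone cannot settle that.

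**The case against.** The strongest case for leaving the covariate in has four parts.

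1. **The protocol does not call the interval a baseline variable.** A reader might infer that the sentence contradicts itself by listing the interval under baseline differences. It does not: the interval stands in its own clause, as a second thing to be adjusted for. This part stands, and no internal contradiction is claimed.
2. **A large difference between arms is unlikely.** Both arms share one schedule, masked interviewers do the visits, and practitioner contact is capped at 6 hours. Nothing in the protocol shows that this contact delays a 26-week interview. A reader might enter r = 0.3 and d_T = 0.5 and conclude that half the target effect (0.15 SD) is at risk, or that the covariate as such undoes randomisation. The documents support neither inference. This part stands, and it limits the size of the point.
3. **Time matters in a progressive disease.** If the arms differ only through scheduling, adjustment removes an artefact and dropping the term leaves it in. This stands too, and is a real cost of the change.
4. **The term may exist for the pilot.** If the interval means only the changed pilot schedule, it is fixed by design and harmless. That is possible, but the article does not make the link, and the wording as it stands covers the interval for every participant.

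It might also seem natural to replace the covariate with a fixed window around 26 weeks. If late interviews were excluded, this would select on the same post-randomisation variable, so it is not the remedy. That the article states no window is not a fault either, since such detail commonly sits in the analysis plan.

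**Conclusion.** The point holds in a limited form. The article fixes a post-randomisation covariate in the primary model, and under credible mechanisms this moves the estimate away from the randomised comparison. For the assumed inputs the shift is about 0.01 to 0.06 SD, or 3% to 20% of the 0.30 target. It is zero if the interval is unrelated to allocation or to outcome. The size rests entirely on r and d_T, which the documents do not give. Given the common schedule and masked interviewers it is probably small, and its direction cannot be predicted. This is an inexpensive improvement to the plan, not a flaw that threatens the trial.

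**What to change.** In Statistical analysis and in the statistical analysis plan, before data are accessed:

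- Restrict the primary ANCOVA of 26-week BADLS to variables measured before randomisation.
- Analyse all 26-week interviews by treatment allocated, without excluding late ones.
- Move the interval-adjusted model to a sensitivity analysis, and report the distribution of the interval by arm.
- If the term was meant to handle the pilot's different schedule, say so. Then use the pilot's 26-week scores, or a pilot/main-study indicator, which is fixed by design.

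The cost is a small change of wording and, at most, a slight loss of precision. If the arms differ only through scheduling, a small timing artefact stays in the primary estimate (0.3 × 0.05 = 0.015 SD under the assumptions above). The sensitivity analysis and the table of intervals by arm would show it.

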### Design

This is a multi-site, pragmatic randomised trial to evaluate the effectiveness and cost-effectiveness of memory aids delivered by Dementia Support Practitioners (DSPs) to people with early-stage dementia relative to treatment as usual (TAU). Pairs of people with mild to moderate dementia and an identified carer will be recruited and allocated at random between the comparator group receiving TAU plus dementia guide [13] and the intervention group receiving TAU plus the DESCANT intervention. The primary outcome measure is the Bristol Activities of Daily Living Scale (BADLS) [14], measured at 13 and 26 weeks (primary end point) after baseline.

To ensure intervention and methods work in practice, a feasibility study and internal pilot was conducted with 40 participants, recruited from two settings in equal numbers. The Acceptance Checklist for Clinical Effectiveness Pilot Trials (ACCEPT) criteria [15] was adapted to assess whether the intervention and the trial protocol work in practice, and the DMEC had accepted these criteria. The only adjustments suggested by the pilot was to reduce the length of follow up from 12 to 6 months in the main study to enable the recruitment targets to be met and reflect the realistic goal of improving BADLS scores over 6 months. Therefore, the pilot data will be included, adjusted to reflect this change in the main analysis. This modification, approved by the University of Manchester as Sponsor, was communicated to the National Research Ethics Service who approved the original protocol (reference 15/NW/0822), sites and participants.

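### Multiple imputation for the 26-week BADLS is used only if predictors of missingness are identified; the trigger should be dropped and the 13-week BADLS always used, although the likely bias is small

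*Protocol article*

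**What the plan says.** Under Statistical analysis, the protocol article sets the end point: "Primary analysis will focus on BADLS scores at 26 weeks". The estimate comes from an analysis by allocated treatment, "using analysis of covariance to adjust for baseline differences in demographic characteristics, comorbidities, time since first attendance at memory clinic or equivalent", and also for the time to follow-up. Baseline BADLS is not among the listed covariates.

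On missing data the same section has two sentences: "Whether the inevitable missing data cause bias will be investigated", and then "If predictors of missing data are identified that are related to outcomes, multiple imputation to adjust for these biases will be used". It does not say how predictors will be sought, what is done if none are found, or which variables would enter the imputation. It refers to a statistical analysis plan, which is not shown.

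Under Design, BADLS is "measured at 13 and 26 weeks (primary end point) after baseline". The Statistical analysis section gives the 13-week score no stated role.

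Under Sample size: "An analysable sample of 360 (180 in each group) across participating Trusts would yield 80% power", and "To allow for 25% attrition (estimated from previous similar studies) between baseline and final interviews the aim is to recruit 480 randomised pairs".

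**The concern.** The conditional rule is stated in the article itself, so an analysis plan that follows the article inherits it. It has two weaknesses.

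- **The trigger is not evidence of no bias.** A search that finds no predictor of missingness may simply have missed one. It is most likely to miss a dependence that differs between arms, because the two arms partly or wholly cancel in a pooled comparison. That is also the kind of dependence that biases a treatment contrast.
- **Observed data may go unused.** A pair seen at 13 weeks but not at 26 weeks has a directly relevant BADLS measurement. Unless imputation is triggered and includes that score, it contributes nothing to the primary estimate.

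Differential loss is plausible. Participants cannot be masked, and one arm has up to 6 hours of practitioner contact. If pairs who are declining leave more often in one arm, the remaining pairs in that arm look better than they should, and the 26-week contrast shifts.

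**Working it through.** **1. The plan's own figures.** For a standardised difference of 0.30, two-sided 5% and 80% power, the normal formula needs n = 2(1.960 + 0.842)²/0.30² ≈ 175 per arm, or 350 in total. With 180 per arm, power is 81%. Recruitment is 360/(1 − 0.25) = 480. Both figures reproduce. I use 480 randomised, as Sample size does; the Abstract's aim of randomising 360 is a separate inconsistency.

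**2. Inputs the documents do not give (assumed).**
- Correlations: baseline to 13 weeks 0.75, baseline to 26 weeks 0.70, 13 to 26 weeks 0.80.
- Loss: 10% before week 13 at random and 15% between weeks 13 and 26, so 216 of 240 per arm have a 13-week score and 180 have a 26-week score.
- Later loss depends on 13-week BADLS through a logistic slope per SD that may differ by arm.
- Trigger: a 5% pooled test of whether 13-week BADLS differs between pairs lost later and pairs retained. If it fires, the 13-week score is used through regression by arm, standing in for imputation. If not, complete cases are used.
- 1,500 simulated trials per setting. With a standard error of about 0.105 per trial, simulation error is about 0.105/√1500 ≈ 0.003 SD.

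**3. Average bias of the conditional rule, in SD.**

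| Dependence of later loss on 13-week BADLS | Trigger fires | With baseline BADLS | Without baseline BADLS |
|---|---|---|---|
| Strong, unequal (slopes 1.0 TAU, 0.2 intervention) | about 99% | about 0 | about 0 |
| Moderate, one arm only (0.5 to 0.7 and 0) | about 43% to 72% | about 0.01 | about 0.03 |
| Opposite directions (0.5 and −0.5) | about 5% | about 0.04 | about 0.12 |
| Equal in both arms | any | about 0 | about 0 |
| None (loss at random) | about 5% | about 0 | about 0 |

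Always using the 13-week score gave bias of about zero in every row.

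**4. Why the residual takes these values.** Average bias ≈ (bias of complete cases when the trigger stays silent) × (1 − firing rate). For the model without baseline BADLS and a 13-to-26-week correlation of 0.80:
- one arm, slope 0.5: 0.064 × (1 − 0.47) = 0.034;
- one arm, slope 0.7: 0.089 × (1 − 0.71) = 0.026;
- opposite directions: 0.132 × (1 − 0.05) = 0.125.

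Against the design effect, 0.01/0.30 = 3%, 0.03/0.30 = 10%, 0.04/0.30 = 13% and 0.12/0.30 = 40%.

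**5. Precision when there is no bias.** With monotone loss, using the 13-week score multiplies the effective sample size by 1/[1 − r²(1 − n26/n13)], where r is the 13-to-26-week correlation given the covariates.
- With baseline BADLS in the model, r = (0.80 − 0.75 × 0.70)/√[(1 − 0.75²)(1 − 0.70²)] = 0.275/0.472 = 0.58. The factor is 1/[1 − 0.339 × (1 − 180/216)] = 1.06.
- Without it, r = 0.80 and the factor is 1/[1 − 0.64/6] = 1.12.
- Over r from 0.5 to 0.8, and 25% to 100% of lost pairs having a 13-week score, effective n per arm is 184 to 214. Power is 82% to 87%, against 81% from complete cases.

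**The case against.** The strongest reply is that bias calculated for complete cases is not the bias of this plan. In the strong, unequal scenario above, complete cases alone give 0.26 with baseline BADLS and 0.19 without it, against a true 0.30, and a spurious 0.04 to 0.11 when there is no effect. A reader might infer that the trial faces errors of that size. The documents do not support this: a scenario so strong would almost always meet the article's own condition for imputation, and the conditional rule then averages 0.30. This reply stands and sets the size given here. It does assume that the 13-week score is among the predictors examined and enters the imputation, which the article neither requires nor excludes.

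Other replies stand in part.
- The article does not name a significance test. The 5% screen is my assumption; a more generous search would fire more often.
- A reader might infer that complete-case analysis is the declared primary method, or that 13-week data are barred. Neither is stated. Focusing on 26 weeks names the end point, and Economic evaluation mentions complete cases only as a variation. The default is inferred from an ANCOVA on 26-week scores, adjusted for time to follow-up, and from Sample size treating the 360 pairs left after attrition as analysable.
- A reader might infer freedom to pick the more favourable result. Governance arrangements has the monitoring committee approve a blinded primary analysis before the analysis team is unblinded, which limits that. It does not make a weak screen reliable.
- The unseen analysis plan may supply the predictors, default and imputation model. Their absence from an article is no fault. The conditional rule, however, is what the article states.
- Baseline BADLS may be missing from the covariate list only through condensation, so both versions are shown.

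**Conclusion.** The point holds as a modest, inexpensive improvement. The article fixes a data-dependent switch between two estimators, and a silent trigger does not justify complete cases. Under the stated assumptions the average bias left by the rule is about 0.01 SD for moderate one-arm dependence and about 0.04 SD for opposite dependence. Without baseline BADLS in the model these become about 0.03 and 0.12 SD. The largest figure needs both opposite dependence and no baseline adjustment. Where loss is unrelated to the 13-week score, or equally related in both arms, bias is about zero. The cost is then precision only: about 6% in variance with baseline BADLS in the model and about 12% without.

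The documents give no correlations, dropout timing or dropout mechanism, and 25% is a planning figure, so these values show scale and are not predictions. Nor does the point imply a shortage of power: 480 randomised with 25% loss still leaves the planned 360.

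**What to change.** Remove the condition and prespecify one primary method that always uses the 13-week BADLS. Either of these would serve:
- a likelihood-based repeated-measures model for the 13- and 26-week scores, with arm by time, baseline BADLS and the stratification factors, and the 26-week contrast as primary;
- multiple imputation by arm, including baseline and 13-week BADLS, followed by the planned ANCOVA.

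Keep the complete-case ANCOVA as a sensitivity analysis. Add a delta-shift analysis that worsens the missing 26-week values by stated amounts, separately by arm. The investigation of predictors of missingness can stay as description and to inform sensitivity analyses, but should not choose the primary estimator.

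The cost is a few lines of analysis-plan wording, settled before data are accessed, and slightly more analysis work. End point, visits and sample size do not change. The drawback is reliance on a missing-at-random assumption, which the conditional imputation already makes.
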